### Participant Timeline

Recruitment will be conducted over a 6-month period starting from February 2024 and ending in July 2024. Recruitment goals will be recorded using the case tracking form up until a final disposition is made. As soon as participants contact OB, they will receive a participant information sheet (PIS) and schedule a time to provide consent. The informed consent process will take 10 minutes via Microsoft Teams, during which the participant will be able to ask questions, and written informed consent can be completed on their behalf. An additional 5 minutes is needed to screen the participant for eligibility. Eligible participants will then complete baseline measures for SI, anxiety, depression, and PTSD, which should take 15 minutes. This entire process should take no longer than 30 minutes. As part of the study’s safety protocol, participants will be contacted at week 3 and 6 to assess their level of SI, which should only take 5 minutes. After 6 weeks, a prearranged web-based meeting will be held via Microsoft Teams to take postintervention measures of SI, anxiety, depression, and PTSD, which should require 15 minutes to complete. Intervention participants will also be sent an email to schedule a date for an interview within 1 week of completing the intervention. The interview will be held via Microsoft Teams, which should take 45-60 minutes to complete.

### Sample Size

The study aims to recruit 30 male or female Syrian asylum seekers and refugees in the United Kingdom, aged 18 years and older, with at least a score of 1 on the C-SSRS [38]. To assess the acceptability of the intervention, at least 12 eligible participants must be recruited for the intervention and postintervention interviews within 6 months (February to July 2024). This number was chosen to enable data saturation for the acceptability and suitability interview at 7 participants while compensating for expected attrition. Since the target population are minorities in the United Kingdom, recruitment is expected to have a lower yield within the allocated time period. If possible, participants will be stratified for sex (male: n=6 and female: n=6), major ethnic groups (Arab: n=10 and Kurdish: n=2), and age (18-39 years: n=10 and 40 years and older: n=2). The National Center for Complementary and Integrative Health notes that sample sizes should be based on practical considerations, including participant flow, financial constraints, and the number of participants needed to evaluate feasibility goals [44]. For qualitative work, 30 or less participants are enough to reach saturation.

### Recruitment

As mentioned before, Eylem et al [22] were unable to recruit enough participants for an RCT and therefore recommended task-shifting to lay people associated with the target population. Task-shifting recruitment to community-based health workers and volunteers has shown to improve recruitment and access for minority ethnic groups [45,46] and was also suggested to scale up mental health interventions for Syrian refugees in the Middle East and Europe [47]. Thus, participants will be recruited via cultural brokers as well as NGOs, charities, local councils, and social media.

The study will use purposive sampling to recruit participants from various demographic backgrounds including age, gender, religion, ethnicity, and refugee status. All recruitment will be via the web using a study advertisement or email correspondence, which will outline the purpose and development of the intervention. OB will be responsible for all direct communication with participants and external individuals and organizations involved in sharing information about the study. The recruitment process will be recorded using an eCTF in accordance with the 8-step guidelines of Stewart et al [37], which includes tracking the sources of potential participants (NGOs, charities, local councils, and social media), the number of participants recruited within the set time period (60 in 6 months), sample characteristics (age, gender, ethnicity, and religion), and reasons for loss at each stage (consent, eligibility, randomization, waiting list, intervention, and interview). No incentives for participation will be provided other than access to the intervention.

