##### Secondary Outcomes

Secondary outcomes include the feasibility of recruitment goals and measurement instruments. Recruitment goals will be tracked in accordance with the guidelines by Stewart et al [37] for diverse populations. This will include using an eCTF to track the sources of potential participants (NGOs, charities, and social media), the number of participants recruited within the set time period (30 in 6 months), sample characteristics (age, gender, ethnicity, and religion), and reasons for loss at each stage (consent, eligibility, enrollment, etc).

The feasibility of measurement instruments will be assessed in terms of the number of people who completed questionnaires, the amount of information missing, which should not exceed 10%, and the time it took to complete them. This will include measuring SI for intervention participants at baseline (T1), after 3 weeks (T2), and post treatment (6 weeks after baseline: T3). Depression, anxiety, and PTSD will also be measured at baseline and post treatment. If possible, all participants who begin the intervention will complete the follow-up assessment at week 6 irrespective of whether they complete the intervention or not. All the data will be recorded on the eCTF. The outcome measures used in the study are as follows:

SI will be measured using the SI subscale of the C-SSRS, which is a 6-item tool used to assess SI [38], which has shown good internal consistency (α=.966) for an Arabic-speaking population [39]. The C-SSRS was chosen due to its compatibility with Syrian’s conceptualization of SI as a wish for death. An answer of yes to any of the 6 questions indicates a presence of SI, and a score of 4 and above indicates serious SI.

Anxiety and depression will be measured with the Hospital Anxiety and Depression Scale (HADS) [40,41]. The Arabic version has shown acceptable internal consistency for both the anxiety (α=.73) and depression scale (α=.77) [42]. HADS consists of 14 items, which are scored on a 4-point Likert scale between 0 and 3. The total score range is between 0 and 21, with scores between 0 to 7 indicating normal anxiety or depression, scores between 8 to 10 indicating borderline abnormal anxiety or depression, and scores above 11 indicating abnormal anxiety or depression.

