##### Quantitative Outcomes

Quantitative feasibility outcomes will be reported descriptively. Recruitment rates will be assessed in terms of the percentage of those contacted who met the eligibility criteria and the percentage of those eligible who were enrolled. Adherence is defined in terms of the number of sessions attended and the time spent completing them. Adherence rates will be calculated as the percentage of all participants who adhered to the intervention. Outcome measure completion rates are defined as the percentage of participants who completed the outcomes and the percentage of the outcomes completed. The feasibility of recruitment methods meeting recruitment goals will also be assessed quantitatively in terms of the percentage of participants recruited from different sources (NGOs, charities, social media, and cultural brokers), the number of participants recruited within the set time period, and the sample characteristics (age, gender, ethnicity, and religion).

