## Results

Recruitment began in February 2024 and will run until 30 participants have been recruited to the study or until the end of July 2024. Thus far, 19 participants have been recruited and provided consent, 16 of whom were eligible, and 12 have completed the postintervention interview. All but one participant were recruited via cultural brokers. The study, including the write-up period, is expected to end in December 2024.

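### The Methods Recruitment section sets the recruitment goal at 60 where the rest of the article says 30; the meaning of *recruited*, the loss stages and the source lists also disagree

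*Protocol article*

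**What the plan says.** Methods, Recruitment describes what the electronic case tracking form will hold. In one sentence it names the sources, "tracking the sources of potential participants (NGOs, charities, local councils, and social media"), the goal, "the number of participants recruited within the set time period (60 in 6 months"), and the losses, "reasons for loss at each stage (consent, eligibility, randomization, waiting list, intervention, and interview").

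Outcomes, Secondary Outcomes describes the same form with a different goal: "the number of participants recruited within the set time period (30 in 6 months"). Its loss stages are consent, eligibility and enrollment, and its sources are NGOs, charities and social media.

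Sample Size says "The study aims to recruit 30 male or female Syrian asylum seekers and refugees in the United Kingdom" and attaches the C-SSRS entry score of at least 1 to those 30. It then requires at least 12 eligible people for the intervention and interviews. The Abstract and the Results both say that recruitment ends at 30 recruited or at the end of July 2024.

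On progress, the Results state "19 participants have been recruited and provided consent, 16 of whom were eligible". The Abstract reports the same people as 19 consented and 16 eligible and enrolled.

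Quantitative Outcomes will report "the percentage of participants recruited from different sources (NGOs, charities, social media, and cultural brokers").

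**The concern.** Whether the recruitment goal is met is a named secondary outcome and the first phase 1 objective. Under step 8 of the guideline adopted in Study Design, a missed goal also leads to modified methods for a larger study. A benchmark with two values, one double the other, cannot be judged met or missed. If exactly 30 people are enrolled, one section calls that full success and another calls it half.

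The unit being counted is also unsettled. Eligibility screening comes after consent (Participant Timeline), so people consented and people eligible are different counts, and the article uses *recruited* for both. That affects conduct as well as reporting, because recruitment closes when 30 have been recruited.

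The remaining mismatches concern the tracking specification: two loss stages that this design cannot produce, and source lists that differ between the tracking and analysis sections.

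**Working it through.** No sample-size formula applies. The study has one group, the feasibility outcomes are descriptive, and the size rests on practical grounds. The check compares sections and takes simple ratios.

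**1. The goal**

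| Section | Goal |
|---|---|
| Abstract, Results | 30, or end of July 2024 |
| Outcomes, Secondary Outcomes | 30 in 6 months |
| Sample Size | 30 |
| Methods, Recruitment | 60 in 6 months |

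The implied pace is 30/6 = 5 per month or 60/6 = 10 per month. No second arm, screening target or attrition factor is stated that would take 30 to 60.

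**2. Progress under each reading** (count ÷ goal; counts from Abstract and Results)

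| Count | Goal 30 | Goal 60 |
|---|---|---|
| 19 consented | 19/30 = 63.3% | 19/60 = 31.7% |
| 16 eligible and enrolled | 16/30 = 53.3% | 16/60 = 26.7% |

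Enrolling exactly 30 would be 30/30 = 100% or 30/60 = 50%.

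**3. Which count ends recruitment at 30**

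- Observed eligibility among the consented: 16/19 = 84.2%.
- If 30 consents end recruitment and that rate holds: 30 × 16/19 = 25.3, about 25 eligible, some 5 fewer than 30.
- Without assuming a rate: 30 − 19 = 11 consents remain, so the eligible total lies between 16 (none of the 11 eligible) and 16 + 11 = 27 (all eligible). Even at best it falls short of 30.
- If 30 eligible and enrolled people end recruitment, no such shortfall is built in.

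**4. Loss stages**

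Methods, Recruitment includes randomization and waiting list. Study Design describes a single-group, noncontrolled study, and Assignment of Interventions says randomization was not considered. Those two stages can never be filled.

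**5. Sources**

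| Section | Cultural brokers | Local councils | NGOs, charities, social media |
|---|---|---|---|
| Outcomes, Secondary Outcomes (tracking) | no | no | yes |
| Methods, Recruitment (tracking) | no | yes | yes |
| Quantitative Outcomes (analysis) | yes | no | yes |

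None of the three is complete. The Introduction's Recruitment section names all five sources and gives brokers the most weight.

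**The case against.** The strongest reply is that a reader can tell which figure governs. The 60 occurs once, in a parenthesis, in a near-copy of a sentence that elsewhere says 30. Both statements of when recruitment ends say 30, and so does Sample Size. This stands as far as it goes: a reader might infer that the end of recruitment is in doubt between 30 and 60, and the article does not support that. What is in doubt there is the unit counted. The wrong figure nevertheless sits in the sentence that specifies tracking against the goal.

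The reply on *recruited* is that both counts are always shown, that the recruitment rates under Primary Outcomes are defined by stage and do not use the word, and that the stated minimum of 12 eligible people is already exceeded by the 16 enrolled. This also stands. Ending with about 25 rather than 30 would breach no stated criterion, and the 25 extrapolates from 3 ineligible people among 19. The ambiguity is limited to the head-count goal and the point at which recruitment closes.

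Three further inferences are tempting and go too far:

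- That this undermines the main outcome. Acceptability and suitability are primary, and their recruitment component is a 70% rate at each stage; the head count is secondary.
- That recruitment through brokers cannot be evaluated. The form itself is not shown, Quantitative Outcomes includes brokers, and the Results already report that all but one participant came through them. Broker source is evidently being recorded.
- That the 60 and the two stages are left over from a randomised waiting-list design. This is plausible, but the article does not say so and the point does not need it.

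**Conclusion.** The 60 is wrong as written. It conflicts with four other sections, nothing stated reconciles it, and it gives one secondary feasibility outcome two benchmarks that differ by a factor of two. Depending on goal and unit, reported progress is 63%, 53%, 32% or 27%. Randomization and waiting list are also wrong as written for this design.

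The double use of *recruited* is a real but smaller ambiguity. Under the consent reading, recruitment would end with about 25 eligible people if the 16/19 rate persists, and with 27 at most from the reported position. The disagreement among source lists is a minor inconsistency between tracking and analysis, not a loss of the broker data.

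The ratios rest only on the counts in the Abstract and Results. The figure of 25 also assumes a constant eligibility rate.

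**What to change.** - **Goal:** in Methods, Recruitment, replace 60 with 30.
- **Unit:** state once that a person counts as recruited when consented, eligible and enrolled, and that the end of recruitment at 30 uses this count. Reword the Results to 19 consented, 16 eligible and enrolled, as the Abstract already has it. Baseline completion should not be added to the definition while keeping 16 as the count, because the article does not say that all 16 completed baseline.
- **Loss stages:** delete randomization and waiting list. Use consent, eligibility, enrollment, intervention and interview in both sections that describe the form.
- **Sources:** use one list (cultural brokers, NGOs, charities, local councils, social media) in Outcomes, Secondary Outcomes; Methods, Recruitment; and Quantitative Outcomes.

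The cost is a few wording edits, plus an entry on the Excel tracking form if brokers or local councils are not already there. No new data are needed. The Abstract says no data have been analysed, so the benchmark can still be settled before results are judged against it.

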### Assignment of Interventions

Since this is an open-label study, aspects such as randomization and blinding procedures were not considered.

### Data Collection, Management, and Analysis

#### Data Collection Plan

##### Primary Outcomes

In line with the feasibility study by Eylem et al [22] of the same intervention, the acceptability of the intervention to participants will be assessed using one-to-one semistructured interviews in terms of cultural relevance (ie, the familiarity of the therapeutic content to one’s cultural background), cultural appropriateness (ie, appropriateness of the therapeutic content in terms of the Syrian cultural context), and whether participants were satisfied with their experience. Like the previous study [2], participants’ lived experience with the migratory process will form the basis of discussions on cultural relevance and appropriateness.

As mentioned earlier, the suitability of the intervention will be analyzed quantitatively in terms of recruitment and adherence rates. Data will be collected with case tracking forms throughout the intervention and during interviews at the end of the intervention. Self-reported and user analytics adherence rates will assess the acceptability of these adaptations and the need for further adaptations.

##### Secondary Outcomes

Recruitment goals will be tracked in accordance with the guidelines of Stewart et al [37] for diverse populations. The use of their guidelines will not only provide structure to the recruitment process but will enable its replication for future studies.

The feasibility of measurement instruments will involve measuring SI for intervention participants at baseline (T1), after 3 weeks (T2), and post treatment (6 weeks after baseline: T3) and depression, anxiety, and PTSD at T1 and T3. Measurements will all be completed during web-based meetings and recorded on the eCTF.

In total, participants will be assessed using 3 outcome measures: C-SSRS [38], the Arabic version of the HADS [40,41], and the Arabic version of the PCL-5 [43]. The C-SSRS was chosen due to its assessment of both SI and a wish for death as well as its good internal consistency (α= .966) for an Arabic-speaking population [39]. The HADS [40,41] was chosen due to its Arabic version showing acceptable internal consistency for both the anxiety (α=.73) and depression scale (α=.77) [42]. In a previous study, Beuthin et al [2] identified stressors with the asylum process as a major concern for Syrian asylum seekers in the United Kingdom, which could be related to anxiety and depression. Finally, the Arabic version of the PCL-5 has shown high (α=.85) internal consistency [43]. Again, in the study by Beuthin et al [2], several Syrian refugees in the United Kingdom reported being diagnosed with PTSD.

##### Quality Control

All participant data, except for interviews, will be recorded in a separate eCTF, which will be completed in an Excel sheet kept in OneDrive for Business. Data from eCTFs will be added to a joint database for analysis once the participant reaches a final outcome. Interviews will be audio-recorded to ensure accuracy. Once transcribed and translated, the audio recordings will be deleted. At the end of the study, all data will be transferred to the chief investigator.

##### Training

All members of the research team have completed the National Institute for Health and Care Research Good Clinical Practice course as well as internal university training in research integrity and security and data privacy awareness. All intervention coaches will be fluent Arabic speakers with at least a master degree in health sciences. They will be trained by the DPhil researcher (OB) in the purpose and procedures of each intervention component to help answer participant questions and provide feedback on their homework.

#### Data Collection Plan: Retention

##### Participant Retention

To enable retention, obtaining informed consent, eligibility screening, enrollment, and all outcome measures will be completed via Microsoft Teams with the assistance of OB instead of web-based surveys. Participants will be followed throughout the trial, and reasons for nonadherence and withdrawal will be recorded within the eCTF if possible. As mentioned earlier, the intervention has been culturally adapted to improve engagement and understanding [2].

##### Participant Withdrawal

Participants will be informed in the PIS that if they choose to discontinue their participation, information recorded in the eCTF up until discontinuation will be retained. All other data including their contact details and those of their GP surgery, exercises and interview audio recording, and transcriptions and translations will be deleted. Participants who score above the cutoff score (4 and above) on the C-SSRS [39] indicating active SI with some intent to act at T2 (week 3), and T3 (week 6) will be withdrawn. To ensure participation in postintervention interviews, the time and date for the interview will be set with the participant during T2 measurements of SI.

##### Data Management

Original written informed consent forms and outcome measures completed by OB on behalf of the participant will be scanned, and password-protected copies will be sent to the participant via email. These data as well as eligibility screening and data necessary to stratify the postintervention interviews such as ethnicity, gender, and religion will be entered electronically into individual case tracking forms labeled with a unique participant number and held in OneDrive for Business provided by the university. Data from eCTFs will later be added to a joint database for analysis once the participant reaches a final outcome. Interview participants’ audio recordings will be labeled with a unique participant number and stored on OneDrive for Business. They will then be deleted after their transcriptions and translations are uploaded to OneDrive. Participant contact details connected to their unique participant number will be kept in a form on OneDrive for Business throughout their participation and deleted when they reach a final outcome. Access to the uploaded data will only be permitted for the DPhil researcher (OB) and the principal investigator (KB) and upon request to members of the Medical Sciences Interdivisional Research Ethics Committee for the purposes of monitoring and auditing of the research. In accordance with university policy, all nonidentifiable data will be stored for at least 3 years after publication. At the end of the study, OB will transfer all data from university servers to the custodianship of the principal investigator (KB), who will thereon be responsible for data management.

##### Quantitative Outcomes

Quantitative feasibility outcomes will be reported descriptively. Recruitment rates will be assessed in terms of the percentage of those contacted who met the eligibility criteria and the percentage of those eligible who were enrolled. Adherence is defined in terms of the number of sessions attended and the time spent completing them. Adherence rates will be calculated as the percentage of all participants who adhered to the intervention. Outcome measure completion rates are defined as the percentage of participants who completed the outcomes and the percentage of the outcomes completed. The feasibility of recruitment methods meeting recruitment goals will also be assessed quantitatively in terms of the percentage of participants recruited from different sources (NGOs, charities, social media, and cultural brokers), the number of participants recruited within the set time period, and the sample characteristics (age, gender, ethnicity, and religion).

